## Methods/Design

### Study setting

Individuals followed at the Evandro Chagas National Institute of Infectious Diseases (INI) of the Oswaldo Cruz Foundation (Fiocruz) will be invited during a medical appointment to participate in the AMIO-CHAGAS study. INI-Fiocruz, located in Rio de Janeiro, Brazil, is a national referral center for the treatment and research of infectious and tropical diseases within the framework of the Brazilian Unified Health System (SUS). INI-Fiocruz receives patients from across the country and provides comprehensive, multidisciplinary care for individuals with CD [21]. Patients currently living in the state of Rio de Janeiro with suspected or confirmed CD are referred to INI for diagnostic investigation or specialized healthcare. Many of these patients are migrants from endemic rural areas. The INI staff includes infectious disease specialists, cardiologists, gastroenterologists, nurses, nutritionists, pharmacists, and physical therapists or exercise physiologists. Patients routinely undergo blood tests, echocardiography (ECHO), electrocardiogram (ECG), 24-hour Holter monitoring, exercise testing, and cardiopulmonary exercise testing, all of which are available at this center. Data from medical records will be collected using standardized protocols. In the event of inconsistencies, records will be reviewed independently by two examiners. Only data with confirmed consistency will be included in the analyses.

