**Methods/Design:**

This is a mixed (retrospective and prospective) longitudinal observational study enrolling 90 patients who will be recruited from a reference center for CD in Brazil. Patients with CCC receiving AMIO will be compared with those not receiving the drug. AMIO was prescribed at the discretion of the treating physician, independently of the present study. Eligible participants will be invited to participate during routine medical appointments. Clinical data, including electrocardiographic and echocardiographic parameters obtained during routine follow-up, will be retrospectively extracted from medical records. Blood samples will be collected at predetermined time points. The primary endpoint will be the inflammatory profile and serological reactivity to anti-*T. cruzi* in CCC patients. Secondary endpoints will include: (**1**) cardiovascular events; (**2**) CCC progression; (**3**) implantable cardioverter-defibrillator (ICD) implantation; (**4**) heart transplantation; (**5**) all-cause death and (**6**) a composite endpoint. The association between AMIO use and longitudinal changes in continuous variables will be determined using mixed linear models. Cox regression analysis will be used to investigate the relationship between AMIO use and selected outcomes (cardiovascular events, CCC progression, and death), adjusted for potential confounders. Hazard ratios (HRs) with 95% confidence intervals (CIs) will be reported.

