### Study design

This is a mixed (retrospective and prospective) longitudinal observational study designed to evaluate the association between chronic use of amiodarone (AMIO) and the following:

(I)**Primary outcome:** inflammatory profile, serologic reactivity to anti-*T. cruzi* antibody, and parasitic load;(II)**Secondary outcomes:** cardiovascular events (new sustained atrial arrhythmias, new sustained or non-sustained ventricular tachyarrhythmias, stroke, heart failure, atrioventricular block, and cardiovascular hospital admissions), CCC progression, internal cardioverter-defibrillator (ICD) implantation, heart transplantation, all-cause death, and a composite endpoint (including the aforementioned cardiovascular events, disease progression, ICD implantation, heart transplantation, and death).

Patients with CCC who take AMIO (exposed group) will be compared with those who do not take this drug (non-exposed group). To minimize potential confounding, patients will be matched based on the stage of CCC according to the Brazilian Consensus on Chagas Disease (A and B1 *versus* B2 and C), age (<50 years *versus* >50 years), and sex (female *versus* male) [15].

Clinical and laboratory data including blood tests, ECG, transthoracic two-dimensional echocardiography (ECHO), and 24-hour Holter monitoring, will be evaluated at three different time points:

(i)**Retrospective data**: from up to 3 years before the start of the study;(ii)**Baseline/recruitment**: at the time of inclusion in the study;(iii)**Prospective data**: during the 2 years of follow-up after recruitment;

The duration of the study, totaling five years of clinical follow-up, was established considering the CCC progresses at a rate of approximately 2% per year [22]. At recruitment, blood samples will be collected for biochemical and molecular analyses to obtain information related to the study’s primary outcome (Table 1) (Fig 1).

**Table 1 pone.0347305.t001:** AMIO-CHAGAS’s study Chronogram: Enrollment, Interventions and Outcome Assessments.

			Retrospective data	Recruitment	Prospective data
			2020 −2022	2023 - 2025	2025 - 2027
**Primary outcome:**	**Immunomodulatory effect**	Gene expression of CCC progression biomarkers in PBMCs	**–**	**x**	**–**
		Determination of serum levels of cytokines and nitric oxide	**–**	**x**	**–**
	**Trypanocidal effect**	Determination of anti-*T. cruzi* antibody titers	**–**	**x**	**–**
		*T. cruzi*-antigen quantification	**–**	**x**	**–**

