### Electrocardiogram, two-dimensional transthoracic echocardiogram, 24-hour Holter and blood pressure

All analyses will be performed annually by Lapclin-Chagas (INI), by qualified professionals. The 12-lead electrocardiogram will be conducted with patients at rest, using a long recording on D2 to assess arrhythmias. The presence or absence of electrocardiographic changes will be determined according to the criteria recommended by the II Brazilian Consensus on Chagas Disease [15]. Electrocardiographic analysis will be performed using the Holter system (portable three-channel recorder and analyzer; Cardio Light® and CardioSmart® 5.0, Cardio System, São Paulo, Brazil), with three channels connected continuously for 24 hours at a rate of 200 samples per second, to detect arrhythmias predictive of mortality and to obtain the arrhythmogenic profile [29,30]. Two-dimensional transthoracic echocardiography will be performed using a phased-array ultrasound system (Philips CVx, USA) equipped with an M4S transducer, following the recommendations of the World Heart Federation [31]. Left ventricular systolic ejection fraction (LVEF), as well as left ventricular diastolic and systolic volumes, will be quantified using Simpson’s biplane method of discs. Assessments will also include left ventricular diastolic function, right ventricular (RV) systolic function, and strain parameters of the left atrium (LA), RV, and left ventricle (LV), to provide a comprehensive evaluation of cardiac mechanics. All measurements will be performed by experienced cardiologists blinded to the clinical data to minimize bias. Blood pressure will be measured on the left arm with participants seated in a quiet room after 5 minutes of rest, using an Omron digital sphygmomanometer.

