### Statistical analysis

Descriptive statistics were used to summarize the characteristics of the study population. Continuous variables will be presented as medians and interquartile ranges (IQR), and categorical variables as absolute and relative frequencies. Missing data will be assessed for their pattern and mechanism (i.e., missing completely at random (MCAR), missing at random (MAR), or missing not at random (MNAR)). The primary approach to handling missing data will be determined once the dataset is available. Depending on the extent and nature of missingness, appropriate strategies may include multiple imputation, complete case analysis, or sensitivity analyses to evaluate the robustness of the findings. The Shapiro-Wilk test will be used to assess the normality of continuous variables. When distributions deviate from normality, appropriate transformations or non-parametric tests will be applied.

Comparisons of patient characteristics according to AMIO use will be evaluated using the independent Student’s t-test for normally distributed continuous variables or the Mann-Whitney U-test for non-normally distributed data. Categorical variables will be compared using the chi-square test or Fisher’s exact test, as appropriate. Correlations between continuous variables related to the primary outcome will be assessed using Pearson or Spearman correlation coefficients, depending on data distribution. AMIO use and longitudinal changes in continuous variables will be analyzed using mixed linear models, adjusted for the duration of amiodarone use. Analyses of time course outcomes (e.g., cardiovascular events, disease progression, all-cause mortality) will be conducted using Cox proportional hazards regression models adjusted for potential confounders such as age, sex, comorbidities and previous etiologic treatment. Hazard ratios (HRs) and their 95% confidence intervals (CI) will be reported. A two-sided p-value ≤ 0.05 will be considered statistically significant.

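### Record-based secondary-endpoint data still unconfirmed after two-examiner review are left out of the analysis, a loss that may depend on outcome and possibly on AMIO use

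*Protocol article*

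**What the plan says.** The rule is in the protocol article under Study setting. It concerns chart data: "Data from medical records will be collected using standardized protocols". Then: "In the event of inconsistencies, records will be reviewed independently by two examiners". Then: "Only data with confirmed consistency will be included in the analyses". The article names no further step for items that the two examiners do not confirm.

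The abstract (Methods/Design) says that clinical data, including ECG and echocardiographic parameters from routine follow-up, "will be retrospectively extracted from medical records". Table 1 takes cardiovascular events from the retrospective and prospective periods, and disease progression from all three periods. Under Statistical analysis, these outcomes go into Cox models.

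Three other statements bear on the point:

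- **Primary outcome.** It does not come from charts: "At recruitment, blood samples will be collected for biochemical and molecular analyses to obtain information related to the study’s primary outcome" (Study design).
- **Blinding.** It is stated once, in the section on ECG, echocardiography, Holter and blood pressure: "All measurements will be performed by experienced cardiologists blinded to the clinical data to minimize bias". Nothing is said either way about the two record examiners.
- **Missing data.** "The primary approach to handling missing data will be determined once the dataset is available" (Statistical analysis). The text does not say whether values excluded under Study setting count as missing.

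**The concern.** An inclusion rule based on confirmed consistency is harmless if inconsistency is unrelated to what is being measured. For several of these endpoints that is doubtful. Death, transplantation and ICD implantation leave little room for disagreement. A short run of ventricular tachycardia, a disputed heart-failure episode or an admission whose cause is recorded differently in two places leaves more. The items most likely to stay unconfirmed are therefore possible endpoint events.

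Exposure may matter too. The endpoint list counts *new* atrial and ventricular arrhythmias, and Study population says that AMIO was prescribed for atrial or ventricular arrhythmias. Exposed patients thus enter with an arrhythmia history, and deciding from a chart whether an episode is new may be harder in them. This is an inference from the article's own endpoint and indication. The article reports no discordance rates.

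A dropped event also need not leave a gap. If the event is removed and the patient's follow-up is kept, the Cox model sees a patient censored without an event. No value is recorded as missing, so a missing-data assessment has nothing to detect.

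**Working it through.** The article gives no figure for discordant or excluded record data, so there is no stated figure to reproduce. The check has three parts.

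**1. Expected events.** Inputs: 45 patients per group (Sample size); progression of about 2% per year and five years of clinical follow-up, of which two are prospective (Study design).

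- Two prospective years: 45 × (1 − 0.98²) = 45 × 0.0396 = 1.8 per group.
- Five years: 45 × (1 − 0.98⁵) = 45 × 0.0961 = 4.3 per group, or 8.6 among all 90.

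The five-year figure is the fairer one, because the article ties the 2% rate to five years and Table 1 also marks progression in the retrospective period. One lost progression is then about 1/4.3 = 23% of a group's expected count. The article gives no rate for the wider cardiovascular events or the composite.

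**2. Effect on the ratio.** The loss fractions are assumptions, and the true ratio is set to 1.00. If lost events count as non-events, the apparent ratio (AMIO / no AMIO) is (1 − loss with AMIO) / (1 − loss without AMIO).

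| Loss with AMIO | Loss without AMIO | Apparent ratio |
|---|---|---|
| 10% | 10% | 0.90/0.90 = 1.00 |
| 30% | 30% | 0.70/0.70 = 1.00 |
| 25% | 10% | 0.75/0.90 = 0.83 |
| 10% | 25% | 0.90/0.75 = 1.20 |
| 30% | 10% | 0.70/0.90 = 0.78 |
| 10% | 30% | 0.90/0.70 = 1.29 |

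If the patients concerned are dropped altogether, the 30% versus 10% case gives 0.79 to 0.85 for assumed event risks of 10% to 40%. The reverse case gives 1.18 to 1.26. The distortion is slightly smaller but of the same kind.

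**3. Effect of equal loss.** Assume a 20% event risk, so 90 × 0.20 = 18 events. Power at a hazard ratio of 0.5 is approximately Φ(|ln 0.5| × √(D/4) − 1.96), where D is the number of events.

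- No loss, D = 18: Φ(1.470 − 1.96) = 31%.
- 20% loss, D = 14.4: Φ(1.315 − 1.96) = 26%.
- 30% loss, D = 12.6: Φ(1.230 − 1.96) = 23%.

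Equal loss therefore leaves the ratio at 1.00 and lowers power that is already low.

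**The case against.** The strongest defence has four parts.

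- **Review comes first.** A reader might infer that any disagreement between sources means deletion. The text does not support that: "records will be reviewed independently by two examiners" describes a resolution step for discordant sources, and only what remains unconfirmed after it is left out. Agreement reached between the examiners might also count as confirmation, and a condensed article may leave such detail to the full protocol. This narrows the point but does not remove it. The exclusion of unconfirmed data is itself stated, and keeping such items would contradict it.
- **Differential loss is not shown.** A reader might infer that AMIO users generate more ECG and Holter records and so more inconsistencies. The article says that these examinations are done annually and as routine, ties their frequency nowhere to AMIO, and matches the groups on stage, age and sex. That route is unsupported. The difficulty of judging a *new* arrhythmia remains plausible, but it is not documented and its direction is unknown.
- **Blinding is not denied.** A reader might infer that the examiners know AMIO status. The article is silent on this, which is not a statement that they are unblinded.
- **Missing data are to be assessed.** The Statistical analysis section names missing-not-at-random data and lists imputation and sensitivity analyses. That could help with an excluded ejection fraction. It does not help with an event that is omitted while the patient's follow-up is kept.

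It is also fair to say that the primary outcome lies outside the rule in practice, that the hard endpoints are little exposed to it, and that the study calls itself exploratory.

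**Conclusion.** The point holds in limited form. As written, the rule leaves out record-based secondary-endpoint data that two examiners cannot confirm, and those are likely to be the ambiguous events. The loss may depend on outcome and possibly on exposure.

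Its size is not known from the document. Under assumed losses of 25% versus 10%, a true ratio of 1.00 appears as 0.83 or 1.20, depending on which group loses more. With equal loss there is no bias under a true null, only fewer events and less power. With about 4.3 expected progressions per group over five years, single events carry weight. A reader who counts only the two prospective years (1.8 per group) might conclude that one deletion halves a group's count, but the article's five-year basis does not support that.

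The change is worth making for the cardiovascular-event, progression and composite analyses. It does not threaten the primary outcome.

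**What to change.** For endpoint data, replace the exclusion rule with the following:

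1. The same two examiners resolve discordant items by consensus, using a fixed source order: the original tracing, image or discharge summary takes precedence over a clinic note.
2. Items still unresolved stay in the dataset, flagged as possible.
3. The main analysis uses confirmed plus consensus events. A sensitivity analysis counts the possible items first as events and then as non-events.
4. The number of possible items is reported by AMIO group, so that readers can see whether the loss would have been differential.
5. The article states whether the examiners know AMIO status. Where feasible, someone other than the examiners withholds it when the records are abstracted. The examiners cannot mask the drug names themselves, since whoever masks them has seen them.

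The cost is a wording change, some extra examiner time and one added analysis. Withholding AMIO status needs another person's time at abstraction, which is why it is asked for only where feasible. Table 1 runs prospective follow-up to 2027, so the change can still cover prospective events.

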### Study design

This is a mixed (retrospective and prospective) longitudinal observational study designed to evaluate the association between chronic use of amiodarone (AMIO) and the following:

(I)**Primary outcome:** inflammatory profile, serologic reactivity to anti-*T. cruzi* antibody, and parasitic load;(II)**Secondary outcomes:** cardiovascular events (new sustained atrial arrhythmias, new sustained or non-sustained ventricular tachyarrhythmias, stroke, heart failure, atrioventricular block, and cardiovascular hospital admissions), CCC progression, internal cardioverter-defibrillator (ICD) implantation, heart transplantation, all-cause death, and a composite endpoint (including the aforementioned cardiovascular events, disease progression, ICD implantation, heart transplantation, and death).

Patients with CCC who take AMIO (exposed group) will be compared with those who do not take this drug (non-exposed group). To minimize potential confounding, patients will be matched based on the stage of CCC according to the Brazilian Consensus on Chagas Disease (A and B1 *versus* B2 and C), age (<50 years *versus* >50 years), and sex (female *versus* male) [15].

Clinical and laboratory data including blood tests, ECG, transthoracic two-dimensional echocardiography (ECHO), and 24-hour Holter monitoring, will be evaluated at three different time points:

(i)**Retrospective data**: from up to 3 years before the start of the study;(ii)**Baseline/recruitment**: at the time of inclusion in the study;(iii)**Prospective data**: during the 2 years of follow-up after recruitment;

The duration of the study, totaling five years of clinical follow-up, was established considering the CCC progresses at a rate of approximately 2% per year [22]. At recruitment, blood samples will be collected for biochemical and molecular analyses to obtain information related to the study’s primary outcome (Table 1) (Fig 1).

**Table 1 pone.0347305.t001:** AMIO-CHAGAS’s study Chronogram: Enrollment, Interventions and Outcome Assessments.

			Retrospective data	Recruitment	Prospective data
			2020 −2022	2023 - 2025	2025 - 2027
**Primary outcome:**	**Immunomodulatory effect**	Gene expression of CCC progression biomarkers in PBMCs	**–**	**x**	**–**
		Determination of serum levels of cytokines and nitric oxide	**–**	**x**	**–**
	**Trypanocidal effect**	Determination of anti-*T. cruzi* antibody titers	**–**	**x**	**–**
		*T. cruzi*-antigen quantification	**–**	**x**	**–**
**Secondary outcomes**:	Cardiovascular events	New sustained atrial arrhythmias and new sustained or non-sustained ventricular tachyarrhythmias, stroke, heart failure, atrioventricular block and cardiovascular hospital admissions	**x**	**–**	**x**
	Disease progression	Monitored by echocardiography (ECHO), electrocardiogram (ECG), 24-hour Holter	**x**	**x**	**x**
	ICD implantation	According to the medical prescription	**–**	**–**	**x**
	Heart transplantation	According to the medical prescription	**–**	**–**	**x**
	Death of all-cause	–	**–**	**–**	**x**
	Composite endpoint	–	**–**	**–**	**x**

CCC: Chronic Chagas cardiomyopathy; ECG: Electrocardiogram; ECHO: Echocardiography; ICD: Implantable cardioverter-defibrillator; PBMCs: Peripheral blood mononuclear cells.

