Amiodarone (AMIO) is the most commonly used antiarrhythmic drug in CCC primarily prescribed for abnormalities in the cardiac conduction system [12], and is considered effective in reducing both atrial and ventricular arrhythmias [15,16]. This drug is a class III antiarrhythmic according to the Vaughan Williams classification, and its mechanisms of action include inhibition of potassium, calcium, and sodium channels, thereby prolonging the plateau of the cardiac cell action potential [17,18]. Due to the scarcity of studies involving individuals with CD, the use of AMIO in patients with CCC is based on an expected benefit that should outweigh its adverse effects, such as pulmonary toxicity, polyneuropathy, gastrointestinal discomfort, bradycardia, hepatotoxicity, thyroid dysfunction, and ocular complications [15,19,20]. Therefore, this study will evaluate the potential benefits associated with the use of AMIO in patients with CCC, including possible trypanocidal and immunomodulatory effects of this antiarrhythmic drug.

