### Study population

Participant recruitment began on March 7, 2023, and is expected to be completed by December 2025. Participants are being recruited sequentially during their routine medical visits. Patients using AMIO are identified from the database of individuals monitored by the Clinical Research Laboratory on Chagas Disease at INI-Fiocruz. Only patients who have been receiving AMIO for at least three months will be included, ensuring adequate tissue impregnation with a cumulative dose of 10 g [23].

Inclusion criteria are as follows:

Confirmed diagnosis of CD, based on two serological tests with different methodologies (enzyme-linked immunosorbent assay [ELISA] and chemiluminescence) [14,15];Individuals over 18 years of age;Patients classified within the following CCC stages: A, B1, B2, and C [15].

Exclusion criteria are as follows:

Co-infection (HIV, hepatitis B and C, HTLV, Hansen’s disease, leishmaniasis and paracoccidioidomycosis);Immunosuppression of any nature;Cancer;Patients with stage D of CCC will be excluded due to their complex clinical management, including frequent hospitalizations and medication adjustments, which could affect the study’s feasibility.

Patients meeting the inclusion criteria will be invited to participate in the study, and written informed consent will be obtained from all individuals who agree to enroll.

Importantly, AMIO use was prescribed at medical discretion to treat atrial or ventricular arrhythmias [12], independently of this study, characterizing an observational study design.

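### The new-arrhythmia component of the cardiovascular-event endpoint is not comparable between AMIO users and non-users, and the net direction of the bias is unknown

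*Protocol article*

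**What the plan says.** All references are to the protocol article.

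- **Endpoint (Study design; Table 1).** The cardiovascular-event outcome contains "new sustained atrial arrhythmias, new sustained or non-sustained ventricular tachyarrhythmias" and, beside them, "stroke, heart failure, atrioventricular block, and cardiovascular hospital admissions". Only the arrhythmia items carry the word *new*, and it is not defined. The composite includes these cardiovascular events.
- **Exposed group (Study population).** "AMIO use was prescribed at medical discretion to treat atrial or ventricular arrhythmias". These are prevalent users: "Only patients who have been receiving AMIO for at least three months will be included".
- **Non-exposed group (Study population; Study design).** No arrhythmia is required for entry. The article says "patients will be matched based on the stage of CCC according to the Brazilian Consensus on Chagas Disease", and also on age and sex; arrhythmia history is not a factor.
- **Model (Statistical analysis).** Event outcomes go into "Cox proportional hazards regression models adjusted for potential confounders such as age, sex, comorbidities and previous etiologic treatment". Baseline arrhythmia is not named, and no restriction to patients at risk is stated.
- **Window (Table 1).** Cardiovascular events are marked for the retrospective and the prospective period. The composite is marked for the prospective period only.

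**The concern.** Whether a patient can score the arrhythmia component depends on arrhythmia history, and arrhythmia history also determines who receives AMIO. Neither the matching nor the named covariates separate the two.

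Suppose *new* means not previously present. A patient who already has a qualifying atrial arrhythmia then cannot score the atrial class, and likewise for the ventricular class. Left in the risk set, that patient supplies person-time in which the event cannot occur. A covariate does not repair this, because the hazard for that class is zero by definition.

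Suppose instead that *new* means a new episode. The structural zero disappears, but patients with a prior arrhythmia carry a recurrence risk that the plan does not balance.

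Under either reading, the hazard ratio for this component mixes any drug effect with the difference in arrhythmia history. That mixture passes into the cardiovascular-event endpoint and the composite.

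**Working it through.** The plan states no event rate, no share of patients with prior arrhythmia and no expected hazard ratio, so there is no planned figure to reproduce. From the documents come 45 patients per group (Sample size) and 2 years of prospective follow-up (Study design). Every other input below is an assumption, and the true effect of AMIO is set to none throughout.

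**1. Arrhythmia component, prospective, first-ever reading.** Let f and g be the shares of users and non-users who cannot score a new arrhythmia. The apparent risk ratio is (1 − f)/(1 − g).

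- f = 0.25, g = 0.20: 0.75/0.80 = 0.94
- f = 0.50, g = 0.20: 0.50/0.80 = 0.62
- f = 0.75, g = 0.20: 0.25/0.80 = 0.31
- f = 0.25, g = 0.40: 0.75/0.60 = 1.25

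**2. Same reading, one class blocked only.** A patient with a prior atrial arrhythmia can still score a ventricular one. Take equal hazards of 5% per year per class, a share q = 0.7 of users with one class blocked, and no non-user blocked. The rate ratio is 1 − q/2 = 0.65. Expected two-year counts are:

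- non-users: 45 × (1 − e^−0.2) = 8.2
- users: 45 × [0.7 × (1 − e^−0.1) + 0.3 × (1 − e^−0.2)] = 5.4

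Setting blocked non-users to zero makes this a one-sided illustration.

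**3. Whole cardiovascular-event endpoint.** Let r be the arrhythmia risk in patients able to score and s the risk of any other component, taken as independent. The ratio is [1 − (1 − (1 − f)r)(1 − s)] / [1 − (1 − (1 − g)r)(1 − s)]. With r = s = 0.20, f = 0.50 and g = 0.20 it is (1 − 0.90 × 0.80)/(1 − 0.84 × 0.80) = 0.280/0.328 = 0.85. With r and s each from 0.10 to 0.30 and g = 0.20, it is 0.74–0.94 at f = 0.50 and 0.53–0.89 at f = 0.75. The other components dilute the artefact but do not remove it.

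**4. Retrospective window.** Let a share h of users have the arrhythmia that led to AMIO counted as an event. For the arrhythmia component the ratio becomes [h + (1 − h)(1 − f)r] / [(1 − g)r]. With f = 0.50, g = 0.20, r = 0.20:

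- h = 0.10: (0.10 + 0.90 × 0.10)/0.16 = 1.19
- h = 0.20: (0.20 + 0.80 × 0.10)/0.16 = 1.75
- break-even: (0.16 − 0.10)/(1 − 0.10) = 0.067, about 7% of users

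Over r of 0.10–0.30 and f of 0.50–1.0, break-even lies between 3% and 24%.

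**5. Confounding by indication, prospective only.** The artefact in step 1 is cancelled if users still at risk have (1 − g)/(1 − f) times the risk of non-users still at risk. With g = 0.20 this is 0.80/0.50 = 1.6 at f = 0.50, and 0.80/0.25 = 3.2 at f = 0.75.

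**The case against.** A reader might infer more: that every AMIO user is barred from scoring, that nearly all the event-free time lies in the AMIO group, and that the drug therefore looks protective by construction. The documents do not support this.

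- *New* is undefined. Under a new-episode reading nobody is barred.
- The treated rhythm need not be a qualifying one. The endpoint needs a sustained atrial arrhythmia or a ventricular tachyarrhythmia, whereas the categorical variables under Data collection include premature beats and extrasystoles. The Background also describes AMIO as "primarily prescribed for abnormalities in the cardiac conduction system", although that is a general statement and the Study population section describes the patients of this study.
- Non-users may have prior arrhythmia too. They have the same disease and are matched on stage, and prevalence is given for neither group.
- Steps 4 and 5 push towards apparent harm and can outweigh step 1.
- The same argument cannot be carried over to ICD implantation, because no difference between groups in existing devices is documented.

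These points stand, and they limit what can be said about direction and size.

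It can also be said that an article leaves the definition of *new* and the risk set to the full protocol or analysis plan, that the covariate list is open-ended, and that the outcome is secondary in a study the Discussion calls exploratory. An undefined term alone would indeed be a detail for another document. But the article does fix the endpoint wording, the matching factors, the selection of users and the model. Taken together, these leave the groups unequal in the very history on which the component depends.

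**Conclusion.** As written, the arrhythmia component is not comparable between users and non-users, and it carries this into the cardiovascular-event endpoint and the composite. The first-ever reading alone lowers the exposed count if, as is probable, prior qualifying arrhythmia is more frequent among users. Recurrence risk, confounding by indication and retrospective counting act the other way. By Table 1, retrospective counting concerns the cardiovascular-event endpoint rather than the composite. The net direction is unknown.

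The size is illustrative only. With no true effect, the component's ratio ranges from 0.31 to 1.25 over the shares tried in step 1. For the whole event endpoint, prospective only and with 20% of non-users unable to score, it ranges from 0.53 to 0.94 for f of 0.50 and 0.75. All shares and rates are assumed. The primary biomarker outcomes are unaffected. The change is worthwhile and cheap, but the point does not undermine the study as a whole.

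**What to change.** - Define *new* as the first qualifying arrhythmia of its class (sustained atrial; sustained or non-sustained ventricular) after recruitment, and start the risk period for this component at recruitment.
- Analyse each class only in patients of both groups with no qualifying arrhythmia of that class on pre-recruitment ECG, Holter or records. The look-back should run to each patient's own recruitment date, since Table 1 places the retrospective data in 2020–2022 and recruitment in 2023–2025.
- Adjust or stratify the cardiovascular-event and composite analyses by baseline arrhythmia type.
- Show a sensitivity version of both endpoints without the arrhythmia components. Making that the main version would redefine two endpoints and drop a component relevant to an antiarrhythmic drug, so it is not proposed.

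The cost is analysis wording and use of ECG and Holter data that the plan already collects; no new visits or patients are needed. The downside is fewer patients and events in the class-specific analyses, hence wider intervals in a study of 90. Restriction also does not remove confounding by indication among the patients who remain at risk.
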